## 3. Discussion

This study protocol describes how the current study will evaluate the impact of the ttC model on the maternal health continuum of care outcomes in Northern Uganda using a cross-sectional quasi-experimental design and employing propensity score matching to control for selection bias [39]. This study will integrate Andersen’s behavioural model, which identifies predisposing, enabling and need-based factors, to obtain a comprehensive understanding of whether emphasizing these factors within the ttC model will result in a more effective maternal health continuum of care outcomes [26]. 

We expect that ttC will significantly improve the maternal health continuum of care outcomes ANC, PoD, and PNC. These outcomes are important to study because they have shown to improve the overall health and wellbeing of both the mother and the child, which reduces the infant and maternal mortality rates globally, thereby contributing to the achievement of Sustainable Development Goal 3 on health and well being [44,45]. Improved ANC utilisation has been linked to early identification of complications, and preventing maternal deaths and comorbid conditions like anaemia [45,46,47]. Ensuring that more women deliver at the advised PoD allows trained professionals to manage both anticipated and unanticipated complications that arise during delivery thereby preventing stillbirths and improving the survival rate of the newborns [48,49]. In addition, since the first days after birth are associated with the highest risks for both the mother and the baby, having PNC visits is essential for the prevention of infection and management of infectious diseases such as HIV and malaria, and maternal anaemia [50,51,52].

This ttC approach, delivered by CHWs to change the maternal care utilisation behaviours of mothers, will likely succeed in the northern Uganda region, which is characterised by inadequate sex education [36], high poverty rates [18], very high teenage pregnancy rates [36], cultural diversity, limited healthcare access, poor health outcomes, and presence of conflict-affected individuals [32]. This is because the ttC approach, as opposed to other available packages, has a distinct advantage of tailoring its message to each household’s characteristics [18,19]. This contextualisation makes the information provided more receptive to the mothers, therefore more relevant and effective as it is relative to their environment, and thus increasing the likelihood of changing behaviours and improving maternal health outcomes. 

Furthermore, adapting Andersen’s behavioural model will give a new perspective on the factors that strongly influence the community, and therefore provide evidence-based insights to emphasize during the modification of the ttC package for use in other conflict-affected regions like northern Uganda [17,18,27].

In conclusion, the evaluation evidence from this impact study is expected to contribute new knowledge on the effects of ttC for similar low-resource and conflict-affected settings [23].

### Strengths and Limitations

This study’s main limitation is the use of a cross-sectional dataset to experiment with an intervention. However, propensity score matching will be used as an alternative to a randomised trial by eliminating the bias due to confounding, and thereby ably applying causal inference for the results [30]. Another limitation would be the several unmeasured confounders which would improve precision if included in the study. This will be mitigated by using sensitivity analysis to sow robustness of the results to these unmeasured confounders [43]. There may be response bias due to self-reporting, which may affect the information gathered. This limitation will be addressed by providing confidentiality assurance to the study participants to allow them to answer more truthfully. Finally, spillover effects will be mitigated by having distant subcounties that do not share borders.

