### 2.3. ttC Intervention

This ttC package has been identified by WHO as the only available global CHW training package that has supporting material that guide country-specific integration, as opposed to other generic packages available that develop capacities of CHW in maternal health [23]. It targets the first 1000 days (pregnancy and postpartum) of a child’s life [18]. Before implementation of the ttC approach, the CHWs were first trained for 5 days using a standardised ttC package. This training was guided by a developed package that outlined the specific tasks CHWs should, the targeted messages to deliver, and the appropriate timing for these messages [18]. 

After training, the CHWs were then grouped and supervised administratively by district health officials who meet them on a monthly basis for support supervision and review of the ttC household register updates. CHWs then identified households with pregnant women or likely households with reproductive-aged women and encouraged them to register and notify the CHW as soon as a pregnancy case occurred [18].

When a pregnancy is identified by the CHW, they visit these households of the pregnant women in a timely manner during the pregnancy and postnatally, with targeted messages to encourage the pregnant women to attend ANC services and plan to give birth in the presence of skilled personnel and attend to PNC. They further encourage male caregivers to be involved in the whole cycle, from pregnancy through birth to nurturing the baby, by providing both emotional and logistical support. CHWs make four visits during pregnancy before birth and seven visits postnatally in the first 2 years after birth, as explained in Table 1, which summarizes and provides a concise and visually organized reference for the key components and objectives of the ttC approach, as adapted from the ttC manual [18]. 

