#### CHW Service Delivery in the Control Subcounty

The CHW in the control subcounty did not follow the ttC approach, but followed the government of Uganda’s national guidelines for recruitment, training, and supervision of CHWs [37]. They were supposed to map out and visit households with pregnant women to ensure that these attended ANC visits and accessed other essential services, but without the timely delivery of targeted messages characteristic of the ttC intervention. They were required to update their CHW registers with progress, which was then reported to the district health officials for supervision. 

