### 2.4. Study Population

The study population/sampling frame is composed of respondents at the household level who will be selected from two subcounties, one with mothers who have given birth between 2 and 12 months of age and who participated in the ttC model sessions (with 876 mothers in the treatment group forming part of the sampling frame), or mothers whose access to ttC sessions was limited to the other subcounty of interest (with 1355 mothers in the control group also forming part of the sampling frame). Thus, the total sampling frame/study population will have 2231 mothers from which the sample will be drawn. The mothers will be recruited from the CHW registers that show that they should have attended counselling sessions during their pregnancy. Inclusion criteria are that the mother had a baby between 2 and 12 months. All other mothers are excluded.

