11th visit at 18 months of life (PNC)	Giving three to four meals to the child a day, child sleeping under a mosquito bed net.

Note: CHW = community health worker, ANC = antenatal care, HIV = human immunodeficiency virus, AIDS = acquired immunodeficiency syndrome, STIs = sexually transmitted infections, PoD = advised place of delivery, PNC = early postnatal care, ttC = timed and targeted counselling.

**Table 2 mps-07-00098-t002:** Study variables and their definitions.

Variable	Definition of Variable	Answering Scale
Intervention Variable		
ttC	This is a behavioural change approach implemented through CHWs to pregnancy households with a wide range of life-saving health practices through appropriately timed messages delivered using interactive storytelling to improve maternal health service utilisation. Mothers will be asked whether they received ttC from a CHW during their pregnancy.	1 = Yes 0 = No
Outcome Variables		
ANC	This is defined as visits to skilled health personnel during pregnancy. Mothers will be asked whether they attended any ANC visits during pregnancy.	1 = Yes 0 = No
PoD	This refers to the advised place of delivery, in a health facility. Mothers will be asked where they gave birth, with answering options including private health facilities, government health facilities, traditional birth attendant’s homes, or their own homes.	1 = Yes 0 = No
PNC	This refers to the care given mothers immediately after birth. This includes at least one PNC visit within the first 6 weeks after delivery. Mothers will be asked whether they visited a health facility for PNC after delivery.	1 = Yes 0 = No
Independent Variables		
Predisposing Factors		
Age	Mothers will be asked for their age at their last birthday.	1 = <20 2 = 21–25 3 = 26–30 4 = 31–35 5 = 36–40 6 = >40
Education level	Mothers will be asked for the highest level of school ever attended.	1. Preschool 2. Primary 3. O Level 4. A level 5. Tertiary 6. University 7. Non
Parity	Mothers will be asked how many births they have had in their lifetime, including the most recent one.	
Marital status	Mothers will be asked for their current marital status.	1. Widowed 2. Married or living together 3. Divorced or separated 4. Never married or never living together
Enabling Factors		
Income level	This refers to the income of the household. Mothers will be asked, on average, what is their approximate maximum monthly.	1. <200,000 2. >200,000–<500,000 3. >500,000–<1,000,000 4. >1,000,000–<2,000,000

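### All three primary outcomes are unverified self-report that may plausibly be inflated more in the ttC arm, and a confidentiality assurance does not deal with a difference between arms

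*Protocol article*

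**What the plan says.** Table 2 defines every primary outcome by a question to the mother.

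- ANC: "Mothers will be asked whether they attended any ANC visits during pregnancy".
- Place of delivery: "Mothers will be asked where they gave birth, with answering options including private health facilities, government health facilities", with traditional birth attendants' homes and her own home as further options.
- PNC: "Mothers will be asked whether they visited a health facility for PNC after delivery".

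Exposure is also asked of her: "Mothers will be asked whether they received ttC from a CHW during their pregnancy".

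On timing, section 2.4 states: "Inclusion criteria are that the mother had a baby between 2 and 12 months". Section 2.3 gives the ttC schedule as four antenatal visits and "seven visits postnatally in the first 2 years after birth". The section on the control subcounty says that CHWs there also visit pregnant households to promote ANC and other essential services, "but without the timely delivery of targeted messages characteristic of the ttC intervention".

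Strengths and Limitations acknowledges response bias from self-report, does not say that it could differ by arm, and gives one remedy: "This limitation will be addressed by providing confidentiality assurance to the study participants to allow them to answer more truthfully".

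**The concern.** The outcomes are the behaviours that ttC teaches mothers to adopt. A mother who has been counselled repeatedly to deliver in a facility and to attend ANC and PNC has more reason to report having done so than a mother who received routine CHW visits. If that happens, part of the Aber-Otwal difference would measure knowledge of the approved answer rather than use of services, and it would run in the direction of the hypothesis.

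The stated remedy addresses a different problem. Confidentiality helps when a respondent fears disclosure to others. It does not make two differently counselled groups report alike.

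**Working it through.** **Is another safeguard stated?**

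- Matching (sections 2.1 and 2.10) uses education, parity, income and age. It balances covariates and cannot correct a wrong outcome value.
- Rosenbaum bounds (section 2.10, gamma 1 to 1.5) concern unobserved confounding, not outcome misclassification.
- The GPS, time-stamp and field checks in section 2.6 target errors or fabrication by data collectors, not untrue answers by mothers.
- The registers in section 2.5 are described as the source of contacts and locations for sampling. No check of outcomes against them, or against facility records, is stated.

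**The plan's own figure.** Section 2.7 uses P1 = 71.5%, P2 = 81.5%, P = 76.5%, z-values 1.96 and 0.842, design effect 1.5 and 10% nonresponse:

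n = 2 × (1.96 + 0.842)² × 0.765 × 0.235 / 0.10² = 282.3; × 1.5 = 423.4; × 1.10 = 465.8. The stated 465 per group reproduces. The effective size per arm is 465 / 1.1 / 1.5 = 282.

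**False difference with no true effect.** Let p be the true proportion in both arms, and f_A and f_O the shares of true non-users in Aber and Otwal who answer yes. Then

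false difference = (f_A − f_O) × (1 − p).

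Only the excess f = f_A − f_O matters. The documents give no value for it, so the values below are assumed. The last column takes f_O = 0 and gives the chance of a significant result favouring ttC at n = 282 per arm (nominal 2.5%).

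| Outcome and source of p | Assumed excess f | False difference (points) | Chance of false positive |
|---|---|---|---|
| Facility delivery, p = 71.5% (section 2.7) | 5% | 0.05 × 28.5 = 1.4 | 5.7% |
| | 10% | 0.10 × 28.5 = 2.9 | 11.5% |
| | 20% | 0.20 × 28.5 = 5.7 | 34% |
| | 35% | 0.35 × 28.5 = 10.0 | 80% |
| PNC, p = 22.5% (Introduction, national) | 5% | 0.05 × 77.5 = 3.9 | 19% |
| | 10% | 0.10 × 77.5 = 7.8 | 55% |
| | 15% | 0.15 × 77.5 = 11.6 | 87% |
| | 20% | 0.20 × 77.5 = 15.5 | 98% |

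Excess needed for a 10-point difference: 10 / 28.5 = 35% for facility delivery and 10 / 77.5 = 12.9% for PNC.

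ANC is not illustrated. Table 2 scores any visit, and the document gives a baseline only for four or more visits (59.9%).

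**If over-reporting is equal in both arms.** A true 10-point difference shrinks to (1 − f) × 10, which is 9.0 points at f = 10%. The bias then works against ttC, so the concern depends on the reporting being differential.

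**The case against.** A reader might infer that ttC mothers are still being counselled on the outcome behaviours when they are interviewed. Table 1 does not support this. The visits labelled ANC or PoD end at 8 to 9 months of pregnancy, and the message on access to postnatal care falls in the first week of life. The visits at 5, 9 and 12 months carry the PNC label but cover infant feeding, supplements, deworming and child development. Mothers interviewed at 2 to 4 months have had none of those three. What the documents support is past counselling plus continuing CHW contact.

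A reader might also infer that only the ttC arm over-reports. The control CHWs' remit speaks against that, and both arms are recruited from CHW registers. More in Aber is defensible; only in Aber is not. Nor can the bias be called likely, since no misreporting rate is given.

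There are partial mitigations. Trained research assistants administer a structured questionnaire, and nothing assigns interviewing to the counselling CHWs. Place of birth is asked as a choice among locations rather than as a yes/no on the advised behaviour. The 10-point yardstick was planned for facility delivery, and applying it to PNC is only illustrative. The response bias itself is disclosed.

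All of this stands and limits the claim. None of it verifies an outcome or makes confidentiality an answer to a difference between arms. Nor is this a detail that a condensed article leaves to the full protocol: the article names the bias and commits to a remedy that does not fit it.

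**Conclusion.** The point holds as a plausible differential reporting bias that the stated remedy does not resolve. The outcomes are unverified, the promoted answers were taught more intensively in Aber, and the direction would favour the hypothesis.

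The size cannot be estimated from the documents. PNC is far more exposed than facility delivery because its non-user share is larger (77.5% against 28.5%): an excess of about 13% would create 10 points for PNC, whereas about 35% would be needed for delivery. These figures assume no true effect and the stated baselines; the false-positive chances also assume the plan's design effect and no over-reporting in Otwal. This does not show that the result will be biased. It is a weakness that can be reduced cheaply, and the change should be made before the questionnaire is final.

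**What to change.** 1. In the Kobo form, where the mother has a card or discharge slip, record ANC contacts, place of birth and PNC date from it, with a source field (record or recall) for each outcome.
2. Pre-specify a record-confirmed sensitivity analysis for each outcome, and report the share with a record by arm. A missing slip cannot be told apart from a birth outside a facility, so unequal availability could itself mislead.
3. For each outcome, report the excess over-reporting in Aber that would remove the estimated effect. With matched proportions a (ttC) and c (control), and none in Otwal, this is (a − c) / (1 − c). At the planned values it is (81.5 − 71.5) / 28.5 = 35%.
4. In Strengths and Limitations, replace the confidentiality sentence with a statement that response bias may differ by arm and could favour ttC, and that confidentiality alone does not resolve it.

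The cost is a few form fields, one extra analysis and one short calculation per outcome. Section 2.5 still foresees a field pretest, where the new fields can be tried. The downside is slightly longer interviews and a smaller record-confirmed set. That mothers hold such cards is an assumption, as the documents do not mention them.

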## Figures and Tables

**Figure 1 mps-07-00098-f001:**
[figure not shown]
The conceptual framework for studying the impact of ttC on the maternal health continuum of care outcomes, adapted from Andersen’s model [25].

**Figure 2 mps-07-00098-f002:**
[figure not shown]
The flow recruitment diagram.

**Table 1 mps-07-00098-t001:** The overview of key components of the ttC approach.

Timing (Outcome Focused On)	Targeted Counselling Given by CHW
1st visit between 2 and 3 months of pregnancy (ANC)	This should be as soon as possible when the mother misses their period so as to encourage the pregnant woman to go for ANC within the first trimester and identify the home care variability in the household that might be needed by the pregnant woman. The CHWs encourage male caregivers to accompany the women for ANCs. They encourage proper nutrition in pregnancy, uptake of iron/folic acid supplements, one extra meal a day for the pregnant woman, handwashing with soap, and having four or more ANCs.
2nd visit between 4 and 5 months of pregnancy (ANC)	This visit occurs at the middle of the pregnancy and is mainly focused on the disease burden, especially on HIV and AIDS, tuberculosis, and other STI testing and prevention awareness.
3rd visit between 6 and 7 months of pregnancy (ANC, PoD)	This visit is meant to promote delivery at a health facility, assisting the family in drawing up a birth plan, including having skilled personnel available during birth, and talk about available family planning measures to encourage 2-year period child spacing.
4th visit between 8 and 9 months of pregnancy (ANC, PoD)	This is one month before delivery to review the birth plan and reiterate the importance of essential newborn care practices. CHW also encourages exclusive breastfeeding and timely seeking for danger signs.
5th visit during the 1st week of life postnatal (PNC)	CHW encourages essential maternal and neonatal care, access to postnatal and postpartum care, and timely seeking for danger signs.
6th visit at 1 month postnatal (PNC)	Growth monitoring, encouraging vaccination against preventable diseases, and care seeking in case of fever.
7th visit at the 5th month of life (PNC)	CHW encourages complementary feeding and the importance of a balanced diet for the baby between the 6th and 9th months.
8th visit at the 9th month of life (PNC)	CHW encourages breast feeding along with complementary foods between the 9th and 12th months, and encourages uptake of micronutrients such as vitamin A supplements.
10th visit at the 12th month of life (PNC)	Encouraging iron rich foods, vitamin A supplements, deworming, and holistic child development.
11th visit at 18 months of life (PNC)	Giving three to four meals to the child a day, child sleeping under a mosquito bed net.

Note: CHW = community health worker, ANC = antenatal care, HIV = human immunodeficiency virus, AIDS = acquired immunodeficiency syndrome, STIs = sexually transmitted infections, PoD = advised place of delivery, PNC = early postnatal care, ttC = timed and targeted counselling.

**Table 2 mps-07-00098-t002:** Study variables and their definitions.

Variable	Definition of Variable	Answering Scale
Intervention Variable		
ttC	This is a behavioural change approach implemented through CHWs to pregnancy households with a wide range of life-saving health practices through appropriately timed messages delivered using interactive storytelling to improve maternal health service utilisation. Mothers will be asked whether they received ttC from a CHW during their pregnancy.	1 = Yes 0 = No
Outcome Variables		
ANC	This is defined as visits to skilled health personnel during pregnancy. Mothers will be asked whether they attended any ANC visits during pregnancy.	1 = Yes 0 = No
PoD	This refers to the advised place of delivery, in a health facility. Mothers will be asked where they gave birth, with answering options including private health facilities, government health facilities, traditional birth attendant’s homes, or their own homes.	1 = Yes 0 = No
PNC	This refers to the care given mothers immediately after birth. This includes at least one PNC visit within the first 6 weeks after delivery. Mothers will be asked whether they visited a health facility for PNC after delivery.	1 = Yes 0 = No
Independent Variables		
Predisposing Factors		
Age	Mothers will be asked for their age at their last birthday.	1 = <20 2 = 21–25 3 = 26–30 4 = 31–35 5 = 36–40 6 = >40
Education level	Mothers will be asked for the highest level of school ever attended.	1. Preschool 2. Primary 3. O Level 4. A level 5. Tertiary 6. University 7. Non
Parity	Mothers will be asked how many births they have had in their lifetime, including the most recent one.	
Marital status	Mothers will be asked for their current marital status.	1. Widowed 2. Married or living together 3. Divorced or separated 4. Never married or never living together
Enabling Factors		
Income level	This refers to the income of the household. Mothers will be asked, on average, what is their approximate maximum monthly.	1. <200,000 2. >200,000–<500,000 3. >500,000–<1,000,000 4. >1,000,000–<2,000,000
Male involvement	This is defined by male caregivers actively supporting their families and caring for their women in order to access better health services. The mothers will be asked whether their partner ever accompanied them to any ANC visits.	1 = Yes 0 = No
Need-based factors		
Presence of chronic illnesses	The mothers will be asked whether they have any chronic health conditions or illnesses (such as diabetes, cancer, HIV/AIDS, kidney/heart disease).	1 = Yes 0 = No
Psychological issues	Mothers will be asked whether they experienced any psychological problems during pregnancy (for example anxiety, depression, stress, body image issues).	1 = Yes 0 = No

Note: ANC = antenatal care, PNC = postnatal care, ttC = timed and targeted counselling, CHW = community health worker, PoD = advised place of delivery, HIV/AIDS = human immunodeficiency virus/acquired immunodeficiency syndrome.

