However, the ANC attendance rate in Uganda is 59.9% for four or more visits [8]. This inadequate utilisation of ANC has been attributed to factors such as long wait times at health facilities, reliance on family or traditional healers for advice, and delayed initiation of care [9]. Compared with home birth, childbirth in a health facility attended by skilled birth attendants is associated with improved maternal and child health outcomes, including lower rates of maternal morbidity and mortality [10,11]. However, in Uganda, only 76.6% of pregnant women deliver in a health facility [12]. The choice for the advised place of delivery (PoD) is often influenced by factors such as social, cultural, and environmental factors [13]. However, regarding Uganda specifically, little is known about factors that influence the use of health facilities for delivery, especially in rural areas [13]. Unfortunately, in Uganda, the knowledge of professionals and policy makers regarding the uptake of early postnatal care (PNC) is also low, hindering the formulation of effective policies aimed at reducing maternal mortality [14]. The first 7 postnatal days account for approximately 65% of maternal deaths, with half (50%) of these deaths occurring within the first postnatal day [15]. However, in Uganda, only approximately 22.5% of new mothers attend at least one PNC visit within six weeks [12].

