### Conceptual Framework

The conceptual framework for this study is based on an adapted Andersen’s Behavioural Model (shown in Figure 1). It shows how maternal health behaviours are influenced by ttC in the presence of various factors proposed by Andersen’s model [25,26]. According to Andersen’s model, predisposing, enabling, and need-based factors affect maternal healthcare utilization [27]. In the current study, predisposing factors include social and demographic factors such as the mother’s age, education level, parity, and marital status. The enabling factors include income level of the household and male involvement in the pregnancy journey. The need-based factors are the presence of chronic illnesses, and psychological issues of the mother. While of importance to the study is the impact of ttC on maternal health behaviours, Andersen’s model helps us to account for how predisposing factors, enabling factors, and need-based factors shape healthcare utilisation. Secondarily, it contributes to understanding the contextual factors influencing maternal health outcomes, which supports efforts to address healthcare access inequality and inform policy development for more equitable access to care [25,26]. 

In this study, we shall incorporate Andersen’s model in investigating the impact of ttC (as an intervention) on ANC utilisation, PoD, and PNC. The ttC is hypothesised to influence maternal healthcare utilisation across the above three aspects by improving mothers’ knowledge on the benefits of fast and sufficient ANC visits, thus improving their attitudes towards ANC. ttC is also hypothesized to improve male-involvement, as well as enhancing the mother’s awareness of their health status and history, thereby affecting PoD and creating need for PNC.

**
General Objective
**

The main objective of this study will be to assess the impact of ttC on the maternal health continuum of care outcomes in Northern Uganda.

**
Specific Objectives
**

To investigate the impact of ttC on ANC utilisation among pregnant mothers.To evaluate the impact of ttC on the advised place of delivery among pregnant women.To assess the impact of ttC on PNC utilisation among mothers.

**
Hypotheses
**

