### 2.9. Study Variables

The primary outcome variables for the study of the impact of ttC on the maternal health continuum of care will be ANC utilisation, skilled birth attendance, and PNC. The ttC variable is nominally defined by whether the household received ttC or not as shown in the Table 2.

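### Table 2 scores ANC as any visit versus none, so this primary outcome cannot register the four-visit or first-trimester change that ttC counsels; the PNC question omits the six-week limit of its own definition

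*Protocol article*

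**What the plan says.** **ANC.** Table 2 defines the outcome as contact with skilled personnel in pregnancy, coded 1 = Yes, 0 = No, and describes the item as: "Mothers will be asked whether they attended any ANC visits during pregnancy". Elsewhere the aim is number and timing:
- Table 1, first ttC visit: the CHW encourages ANC in the first trimester and "having four or more ANCs".
- Conceptual Framework: ttC is expected to work by improving knowledge of the "benefits of fast and sufficient ANC visits".
- Introduction: the problem is framed as "the ANC attendance rate in Uganda is 59.9% for four or more visits". No rate for any visit is given.

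**PNC.** One cell of Table 2 holds both the definition, "This includes at least one PNC visit within the first 6 weeks after delivery", and the question, "Mothers will be asked whether they visited a health facility for PNC after delivery". Section 2.4 limits inclusion to mothers of babies aged 2 to 12 months.

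**Delivery.** Section 2.9 says the primary outcomes "will be ANC utilisation, skilled birth attendance, and PNC". Table 2, the objectives and the sample size calculation use place of delivery or facility delivery instead.

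**The concern.** Hypothesis 1 is that ttC raises ANC utilisation. As coded, the outcome changes only when a woman goes from no visit at all to at least one. Extra visits and an earlier first visit, which the intervention explicitly promotes, leave the score unchanged. Control-area CHWs are also meant to see that pregnant women attend ANC (Section 2.3), and mothers in both arms are drawn from CHW registers (Section 2.4). Few women with no visit at all may therefore remain to be moved. A null ANC result would be silent on the four-visit and early-attendance aims.

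For PNC, every respondent is past six weeks when interviewed, so each has had time for a later visit that the question, read literally, would count. The result would also not be comparable with the six-week baseline of 22.5% cited in the Introduction.

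There is one cross-sectional contact. Visit counts and dates that are not asked cannot be recovered at analysis.

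**Working it through.** **1. The plan's own figure (Section 2.7).** Inputs: 71.5% v 81.5% for facility delivery, two-sided 5%, 80% power, design effect 1.5, nonresponse 10%.

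n = 2 × (1.96 + 0.842)² × 0.765 × 0.235 / 0.10² = 282.3. Then 282.3 × 1.5 = 423.4, and 423.4 × 1.10 = 465.8, against 465 stated. The figure reproduces, and this point does not disturb it.

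**2. Effective size and implied effect.** Effective mothers per arm: 465 × 0.9 / 1.5 = 279. (Dividing by 1.1 instead of multiplying by 0.9 gives 282 and changes the powers below by less than one point.) Implied odds ratio: (0.815/0.185) / (0.715/0.285) = 4.405 / 2.509 = 1.756.

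Power = Φ{(d − 1.96 × SE₀) / SE₁}, with d the difference, SE₀ = √[2p̄(1 − p̄)/n] and SE₁ = √[(p₁(1 − p₁) + p₂(1 − p₂))/n].

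**3. ANC as any visit.** The control rate is assumed. The ttC rate is the control odds × 1.756, turned back into a proportion. Example at 90%: 9 × 1.756 = 15.80, and 15.80/16.80 = 94.05%. SE₀ = 0.02294 and SE₁ = 0.02287, so power = Φ(−0.195) = 42%.

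| Control, any visit (assumed) | ttC | Implied gain | Power |
|---|---|---|---|
| 80% | 87.5% | 7.5 points | 68% |
| 85% | 90.9% | 5.9 points | 57% |
| 90% | 94.0% | 4.0 points | 42% |
| 95% | 97.1% | 2.1 points | 24% |
| 97% | 98.3% | 1.3 points | 17% |

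(The last figure is 16.5% from the formula and 16.7% once the small opposite tail is added.) These are the gains the odds ratio implies, not gains the trial could detect with 80% power.

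**4. ANC as four or more visits, control 59.9%.**
- Same odds ratio: 1.494 × 1.756 = 2.623, and 2.623/3.623 = 72.4%, a gain of 12.5 points. Power 88%.
- The plan's 10-point gain: 59.9% v 69.9%. Power about 70%. For 80% power this needs 357 per group before inflation, so 357 × 1.5 × 1.1 = 589 (or 357 × 1.5 / 0.9 = 595) against 465.

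**5. PNC without the six-week limit.** Take true six-week rates of 22.5% (the cited national rate) v 32.5% (a 10-point gain, assumed). Let a share s of mothers without an early visit answer Yes because of a later one. The observed rate is p + s(1 − p).

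| s, equal in both arms | Control | ttC | Difference | Power |
|---|---|---|---|---|
| 0 | 22.5% | 32.5% | 10 points | 75% |
| 20% | 38.0% | 46.0% | 8 points | 48% |
| 40% | 53.5% | 59.5% | 6 points | 30% |

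If s differs by arm, the direction is open. With s = 20% in control and 30% in ttC, the observed rates are 38.0% and 32.5 + 0.3 × 67.5 = 52.75%, a difference of 14.75 points. With s = 30% in control and 20% in ttC, they are 22.5 + 0.3 × 77.5 = 45.75% and 46.0%, a difference of 0.25 points.

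**The case against.** Any-visit attendance is a form of ANC utilisation, and the Introduction also says, in general terms, that ttC should encourage women to attend. This stands: the item measures something relevant, but not the number or timing that Table 1 and the framework single out.

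A reader might infer that the ANC outcome is known to sit near its ceiling and that a null result would say nothing about ttC. The documents do not support that. They give no any-visit rate, and at an assumed 80% or 85% control rate power would be 68% or 57%. The mismatch between outcome and aim needs no ceiling; the power figures do.

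A reader might also infer that PNC likewise cannot show an effect. That is too strong. The six-week window stands in the same Table 2 cell as the question, the note to Table 1 glosses PNC as early care, and the full questionnaire is not shown and may date the visit. If late visits are counted, the contrast is biased, not abolished. Nor is the bias certain to run towards zero: Table 1 labels ttC contacts up to 18 months as PNC, so late Yes answers could be commoner in the ttC arm.

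Finally, the wording of Section 2.9 could be read as a second primary outcome that is never measured. The abstract, objectives, hypotheses, sample size, analysis section and Table 2 all point to place of delivery, so this is a stray label.

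**Conclusion.** The ANC point stands on the text alone. Under the stated coding, a change in visit number or in timing of the first visit cannot appear in the outcome. Its cost in power is conditional: 42% to 17% if any-visit attendance in controls is 90% to 97%, the odds ratio of 1.76 carries over from facility delivery, and 279 effective mothers per arm remain.

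The PNC point is a contradiction between definition and described question. Under equal late reporting of 20% or 40%, power falls from 75% to 48% or 30%; those shares are assumptions without a source. Under unequal reporting the effect could be overstated or understated.

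The ANC item must be changed before fieldwork because the loss is permanent. The PNC item needs its window, and the Section 2.9 term needs correcting.

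**What to change.** In Table 2 and the questionnaire:
- Record the number of ANC visits and the gestational month of the first. Define ANC = 1 as four or more visits, with first-trimester initiation as a supporting outcome.
- Ask when the first PNC visit took place, and code PNC = 1 only if it was within six weeks of delivery.
- In Section 2.9, replace skilled birth attendance with delivery in a health facility.
- State the power of 465 per group for the redefined ANC outcome: about 70% for a 10-point gain from 59.9%, or 88% if the odds ratio of 1.76 holds.

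The cost is a few added or reworded items, which can go in before the field pretest planned in Section 2.5, and some recall error in counts and timing. The redefinition does not by itself secure 80% power on the 10-point scale, and the protocol should say so.
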